### 2.3 Definitions for Primary and Secondary Endpoint Calculations

[Supplementary Table 2](#)

|               | Prognostic reference standard |           |            |           |
|---------------|-------------------------------|-----------|------------|-----------|
|               | Positive                      | Negative  | Ungradable | Total     |
| IDx-DR Result |                               |           |            |           |
| Positive      | PP                     | PN | PU  | DP |
| Negative      | NP                     | NN | NU  | DN |
| Ungradable    | UP                     | UN | UU  | DU |
| Total         | TP                     | TN | TU  | N  |

[figure not shown]

|                     |               |        |             |
|---------------------|---------------|--------|-------------|
| CTMF-SA-DXSDR006-03 | SAP_2.1_clean | Rev. A | Pg. 6 of 16 |
|---------------------|---------------|--------|-------------|

*Endpoints:*

$$\text{Sensitivity} = \frac{PP}{PP+NP}$$

$$\text{Specificity} = \frac{NN}{PN+NN}$$

$$\text{Positive Predictive Value} = \frac{PP}{PP+PN}$$

$$\text{Negative Predictive Value} = \frac{NN}{NP+NN}$$

$$\text{Diagnosibility} = \frac{PP+PN+NP+NN}{TP+TN}$$

*Endpoints considering ungradable eyes:*

$$\text{Sensitivity}_{+u} = \frac{PP}{PP+NP+UP}$$

$$\text{Specificity}_{+u} = \frac{NN}{PN+NN+UN}$$

$$\text{PPV}_{+u} = \frac{PP}{PP+PN+PU}$$

$$\text{NPV}_{+u} = \frac{NN}{NP+NN+NU}$$

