#### 4. Sample size calculations

**Assumptions:** In this study, a minimum of 200 eyes with mtmDR and at least 140 eyes without mtmDR will be enrolled in the main diagnostic performance study; enrollment will be continued until a minimum of 20 vtDR eyes are confirmed to be sufficient and gradable. The device performance will be evaluated per eye. The primary endpoints will be the sensitivity and specificity of IDx-DR paired with the RV700 in detecting mtmDR based on eye-level results when compared to a PRS by three retinal experts.

[figure not shown]

|                     |               |        |             |
|---------------------|---------------|--------|-------------|
| CTMF-SA-DXSDR006-03 | SAP_2.1_clean | Rev. A | Pg. 8 of 16 |
|---------------------|---------------|--------|-------------|

The predicate device, IDx-DR with the NW400, pivotal trial pre-specified null hypotheses for sensitivity and specificity of 75% and 77.5%, respectively; these represent pre-defined non-inferiority margins. The alternative hypotheses were 85.0% for sensitivity and 82.5% for specificity in support of a non-inferiority design. These lower thresholds for performance will be ruled out with one-sided 97.5% confidence bounds.

As this study is intended to support an extension of the IDx-DR labeling to validate a new camera for use with IDx-DR, the performance is expected to be substantially equivalent to the predicate device at the subject-level.

This study will validate the use of a new camera with the same diagnostic algorithm as currently on the market. The proposed sample size maintains a one-sided 97.5% confidence interval that exceeds the predicate device pivotal trial null hypotheses, i.e., a lower confidence limit  $> 75\%$  for sensitivity and  $> 77.5\%$  for specificity which reflects a 5% non-inferiority offset for sensitivity and a 2.5% non-inferiority offset for specificity (see **Supplementary Table 3** columns 1-4). These hypothesis tests were designed specifically to reflect clinically meaningful eye-level outcomes; substantial equivalence is interpreted as non-inferiority

(**Supplementary Table 3** columns 1-4).

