**Supplementary Table 4: Inputs to power calculations for one-sided exact binomial tests**

| Sensitivity                                                                     | Specificity                                                                        |
|----------------------------------------------------------------------------------------|-------------------------------------------------------------------------------------------|
| $H_0: P \leq 0.75$ vs. $H_1: P > 0.75$                                                 | $H_0: P \leq 0.775$ vs. $H_1: P > 0.775$                                                  |
| $p_{baseline} = 0.80$ is the sensitivity target                                        | $p_{baseline} = 0.80$ is the specificity target                                           |
| $p_0 = 0.75$ sensitivity values below 75% are considered inferior to IDx-DR with NW400 | $p_0 = 0.775$ specificity values below 77.5% are considered inferior to IDx-DR with NW400 |
| $p_1 = 0.835$ hypothesized sensitivity of IDx-DR with RV700                            | $p_1 = 0.871$ hypothesized specificity of IDx-DR with RV700                               |

[figure not shown]

| CTMF-SA-DXSDR006-03                                                                                                                                                                   | SAP_2.1_clean                                                                                                                                                                         | Rev. A | Pg. 9 of 16 |
|---------------------------------------------------------------------------------------------------------------------------------------------------------------------------------------|---------------------------------------------------------------------------------------------------------------------------------------------------------------------------------------|--------|-------------|
| $d_0 = -0.05$ non-inferiority difference.
$d_0 = p_0 - p_{baseline}$ and is the maximum distance that may still be considered non-inferior.                                        | $d_0 = -0.025$ non-inferiority difference.
$d_0 = p_0 - p_{baseline}$ and is the maximum distance that may still be considered non-inferior.                                       |        |             |

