| $d_1 = 0.085$ is the difference at which power is calculated. $d_1 = p_1 - p_0$ and is the hypothesized sensitivity value above the non-inferiority threshold                         | $d_1 = 0.096$ is the difference at which power is calculated. $d_1 = p_1 - p_0$ and is the hypothesized specificity value above the non-inferiority threshold                         |        |             |
| n=200 mtmDR(+) eyes                                                                                                                                                                   | n=140 mtmDR(-) eyes                                                                                                                                                                   |        |             |
| Reject $H_0$ for at least 163/200 true positive eyes, or at least 81.2% sensitivity.
Establish superiority for at least 172/200 true positive eyes, or at least 85.7% sensitivity. | Reject $H_0$ for at least 119/140 true negative eyes, or at least 84.6% specificity.
Establish superiority for at least 122/140 true-negative eyes, or at least 86.7% specificity. |        |             |

The mtmDR(+) and mtmDR(-) sample size depends on the WRC findings so the study will enroll to a target of 564 eyes (282 subjects maximum) to ensure sufficient numbers for the sensitivity and specificity analyses. In addition, in order to achieve 200 mtmDR(+) eyes, we anticipate >450 mtmDR(-) eyes will be accrued based on the historical enrollment ratio (1:4). Thus, the specificity power will be increased and the threshold to establish non-inferiority and superiority will be reduced. Similarly, in the event that >200 mtmDR(+) eyes are determined, all eyes will be included. Thus, the plan is to include all recruited subjects in the final analyses in support of the intent to diagnose analysis principle.

Additionally, weighted sampling will be performed by sampling with replacement among eyes with ETDRS levels at least 53 for computing sensitivity, PPV, and NPV in settings with higher prevalence of severe disease. The overweight sampling is expected to achieve similar sensitivity due to the samples being drawn at random from the gradable and sufficient eyes with ETDRS greater than 53. This analysis is being done following discussion with FDA to assess PPV and NPV outcomes in populations with different vision threatening incidence.

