**Baseline Covariates:** Data collection for each eye will include a unique participant identifier plus age in years at exam, sex, race, ethnicity, ocular condition/procedure history, non-ocular comorbid conditions, diabetic status including duration of diagnosis, recent lab tests (HbA1c, fasting glucose). Continuous variables will be summarized using descriptive statistics (means, standard deviations, and quartiles), and nominal variables will be summarized using counts and percentages. Primary endpoints may be reported in stratified analyses by age, sex, and race/ethnicity. Demographic variables will be presented at the subject-level and eye-level according to: (1) not mtmDR or vtDR, (2) mtmDR, and (3) vtDR.

For the weighted sampling, the demographics (means, SDs) will also be repeated to include those subjects with eyes selected from overweight sampling.

**Missing Data:** By design, each eye will be represented in a cell in the crosstabulation depicted in Section 2.3; missing data are not anticipated. Any missing or ungradable data will be displayed; all available eye-level data will be used. The primary endpoints will be assessed where both the PRS and IDx-DR results will be gradable. Secondary “worst case scenario” analysis considers ungradable values within the calculation.

**Statistical Analysis:** A cross-tabulation of IDx-DR results (positive, negative, ungradable) with the results from the reference standard (positive, negative, ungradable) will be presented for the overall sample. The point estimate for each test characteristic will be presented along with the counts of eyes (numerator and denominator) that contribute to the calculation. Should enrichment be implemented, further stratification will report point estimates and counts of eyes (numerator and denominator) by cohort (not enriched, enriched).

Eye-level one-sided 97.5% lower confidence intervals will be computed by the cluster bootstrap approach to account for correlation introduced by taking measurements from both eyes of each subject [12]; specifically:

[figure not shown]

|                     |               |        |              |
|---------------------|---------------|--------|--------------|
| CTMF-SA-DXSDR006-03 | SAP_2.1_clean | Rev. A | Pg. 12 of 16 |
|---------------------|---------------|--------|--------------|

- participants will be stratified by the number of eyes contributing to the analysis (1 or 2) and by the number of eyes with mtmDR(+) (0, 1, or 2)

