#### 7.4. Enrichment Cohort

In order to assure an adequate range of DR conditions in the study population sample, and avoid spectrum bias, for sensitivity and specificity analysis, the primary care study population may be enriched following the pre-specified formal evaluations outlined in the Data Transfer Plan, to ensure a sufficient range of diabetic retinopathy severity within cases. The enrichment cohort will be targeted using HbA1c levels, if needed, and will draw from the same pool of intent to screen subjects as the non-enriched subjects. To avoid excessive enrollment in any one stratum, the totals will be monitored weekly. Participant enrichment will be targeted based on elevated HbA1c, factors which have been shown to be correlated with higher rates of mtmDR among patients with diabetes. No cap will be placed on enriched participants since such participants will be prospectively recruited. The goal will be to recruit enough subjects to satisfy each stratum. If enrollment patterns are not on track with the study's target population after periodic reviews, enrollment at all sites will be adjusted monthly by modifying the HbA1c. Adjustments from this level may be instituted after a periodic review of the stratum enrollments reflecting the number of participants with diabetic retinopathy or diabetic macular edema. Study sites will be notified by the CRO if there is to be a change in the HbA1c thresholds. Once the total number of cases has been projected in alignment with statistical power requirements, then the final adjustments to participant enrollment criteria will be performed.

Monitoring of strata will be performed by the study statistician (without access to IDx-DR results); only available HbA1c, along with FPRC categorization into mtmDR and vtDR, will be visible for each subject included to date. The study statistician will notify the CRO whether updated HbA1c thresholds are needed. Again, once the strata targets for mtmDR and no/mild DR can be projected, the HbA1c thresholds will be locked.

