### 9.1.1 Sample Size, Precision, and Power

Minimum sample sizes of  $n=200$  mtmDR+ eyes and 140 mtmDR- eyes will be required. The predicate device, IDx-DR with the NW400, pivotal trial pre-specified null hypotheses for sensitivity and specificity of 75% and 77.5%, respectively; these represent pre-defined non-inferiority margins. The alternative hypotheses were 85.0% for sensitivity and 82.5% for specificity in support of a non-inferiority design. These lower thresholds for performance will be ruled out with one-sided 97.5% confidence bounds.

As this study is intended to support an extension of the IDx-DR labeling to validate a new camera for use with IDx-DR, the performance is expected to be substantially equivalent to the predicate device at the subject-level.

This study will validate the use of a new camera with the same diagnostic algorithm as currently on the market. The proposed sample size maintains a one-sided 97.5% confidence interval that exceeds the predicate device pivotal trial null hypotheses, i.e., a lower confidence limit >75% for sensitivity and >77.5% for specificity which reflects a 5% non-inferiority offset for sensitivity and a 2.5% non-inferiority offset for specificity (**Supplementary Table 8** columns 1-4). These hypothesis tests were designed specifically to reflect clinically meaningful eye-level outcomes; substantial equivalence is interpreted as non-inferiority (**Supplementary Table 8** columns 1-4).

Supplementary Table 8: Power and Significance Threshold Calculations Summary (minimum sample sizes)

---

**Digital Diagnostics Confidential.** This document is intended for internal use only and may not be disclosed or reproduced in whole, or in part, for external distribution in any form without express written permission of DDx Legal. All hard copies should be checked against the current electronic revision prior to use and destroyed promptly thereafter. All hard copies are considered uncontrolled documents.

|                                 | Sponsor Criteria (Non-inferiority) |          |             |          |
|---------------------------------|------------------------------------|----------|-------------|----------|
|                                 | Sensitivity                        |          | Specificity |          |
|                                 | Power                              | N-I      | Power       | N-I      |

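### The 80% power for sensitivity assumes 200 analysed mtmDR(+) eyes, but the 200 is a reading-center count and the primary analysis drops eyes with no IDx-DR result

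*Combined protocol and SAP*

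**What the plan says.** **Power.** SAP section 4, Supplementary Table 3 (protocol Supplementary Table 8) gives 80% power for sensitivity with N = 200 and for specificity with N = 140. Supplementary Table 4 is titled "Inputs to power calculations for one-sided exact binomial tests" and gives the rejection rules as 163 of 200 and 119 of 140, so all 200 and all 140 eyes stand in the denominators.

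**Who counts the eyes.** The text after Supplementary Table 4 says "The mtmDR(+) and mtmDR(-) sample size depends on the WRC findings". The 200 and 140 are therefore reading-center counts, and the plan calls them minima.

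**What is analysed.** SAP 5.1, Missing Data: "The primary endpoints will be assessed where both the PRS and IDx-DR results will be gradable". The SAP 2.3 formulas agree. Sensitivity is PP/(PP+NP) and specificity is NN/(PN+NN), so the UP and UN cells (reference standard gradable, IDx-DR not) are in neither. The text below Supplementary Table 5 lists IDx-DR ungradable eyes among the reasons for exclusion from the primary sample.

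**Where a gradability condition appears.** SAP section 4 attaches one to the vision-threatening eyes: "enrollment will be continued until a minimum of 20 vtDR eyes are confirmed to be sufficient and gradable". It attaches none to the 200 or the 140.

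**Monitoring.** Protocol 7.4: "Monitoring of strata will be performed by the study statistician (without access to IDx-DR results"). That section shows the statistician only HbA1c and the reading-center category.

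**The concern.** Two different counts are used as one N. Enrolment is steered on eyes the reading center calls positive, while the test is run on the subset for which IDx-DR also returned a result. Each positive eye that ends as insufficient quality takes one from the denominator on which the 80% rests.

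The loss cannot be taken as zero. The camera is handheld, the operators have no previous fundus imaging experience, and dilation is used only after three failed attempts. Diagnosability is itself a secondary endpoint, so the rate is something the study will measure. Supplementary Table 5 removes further participants for protocol deviations.

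At stake is whether the stated power describes the analysis that will be done. If it does not, the chance of missing the sensitivity target is somewhat higher than the sponsor believes, and the strata data described in protocol 7.4 would not show it.

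**Working it through.** **Inputs from the documents**
- One-sided alpha 0.025 (SAP section 4: "These lower thresholds for performance will be ruled out with one-sided 97.5% confidence bounds").
- Sensitivity: p0 = 0.75, p1 = 0.835, n = 200. Specificity: p0 = 0.775, p1 = 0.871, n = 140 (Supplementary Tables 3 and 4).
- Enrolment target 564 eyes (282 subjects maximum), historical ratio 1:4, more than 450 mtmDR(-) eyes anticipated (text after Supplementary Table 4).

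**Assumed input**
- The share u of reference-standard-gradable eyes with no IDx-DR result. The documents give no figure; the range taken is 5% to 20%.

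**Method.** For each n, find the smallest r with P(X ≥ r | n, p0) ≤ 0.025. Power is then P(X ≥ r | n, p1). Eyes are treated as independent, as in the plan's tables.

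**Step 1. Reproduce the plan.**
- Sensitivity, n = 200: r = 163, actual alpha 0.0182, power 80.6%.
- Specificity, n = 140: r = 119, actual alpha 0.0181, power 80.9%.

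Both critical counts match Supplementary Table 4, and both powers agree with the stated 80%.

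**Step 2. Sensitivity with n = 200 × (1 − u).**

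| Assumed loss | Eyes analysed | r | Power |
|---|---|---|---|
| 0% | 200 | 163 | 80.6% |
| 5% | 190 | 155 | 79.4% |
| 10% | 180 | 147 | 78.0% |
| 15% | 170 | 139 | 76.6% |
| 20% | 160 | 131 | 75.0% |

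**Step 3. Allow for the saw-tooth.** Because r is a whole number, exact power does not fall smoothly. It is 83.2% at 197 eyes, 79.1% at 196, 81.2% at 188 and 80.6% at 183. From 182 eyes down to 100, it is below 80% at every n. Since 182/200 = 0.91, that range starts at a loss of 9%. Below 9%, the result depends on the exact n.

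**Step 4. Is a surplus of positive eyes planned?** At 1:4, 564 eyes give 564/5 ≈ 113 positives and 451 negatives. Conversely, 200 positives plus 450 negatives make 650 eyes, more than 564. These figures do not fit together, and neither shows a reserve of positive eyes above 200.

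**Step 5. Specificity at the expected negatives.**
- 450 less 10% = 405 eyes: power 99.9%.
- 564 − 200 = 364, less 10% = 328 eyes: power 99.5%.
- Analysed negatives fall below 140 only if 1 − 140/450 = 69%, or 1 − 140/364 = 62%, of them have no result.
- Only at the bare minimum would it matter: 140 less 10% = 126 eyes gives 73.2%.

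**The case against.** **The 200 is a minimum, and all further eyes are included.** This is correct, and the plan says its 564-eye target is meant to ensure sufficient numbers. If positives well exceed 200, the problem disappears. But Step 4 shows that the plan's own figures give no such surplus, and nothing describes the target as an allowance for ungradable eyes.

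**The effect is small and the rate unknown.** Also correct. The fall from 80.6% is 2.6 points at 10% loss, 4.0 at 15% and 5.6 at 20%. Quality feedback to the operator, three further attempts after dilation, the diagnosability endpoint and the worst-case analysis all address ungradable eyes. They limit or describe the loss but do not put it into the power calculation.

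**Stronger readings that the documents do not support**
- A reader might infer that power falls short on both endpoints. At the expected number of negatives, specificity power stays above 99% after a 10% loss. A joint power built on 140 negatives less losses would therefore mislead.
- A reader might infer that 80% is lost as soon as one positive eye has no result. The saw-tooth refutes this: 199 eyes give 81.5%.
- A reader might infer that nobody can know how many eyes are analysable. Protocol 7.4 restricts the statistician's view and locks HbA1c thresholds, not enrolment itself. Operators see every insufficient-quality message, and the Data Transfer Plan, which holds the enrichment details, is not among the documents.
- The vision-threatening condition is a weaker contrast than it looks. SAP 3.1 words it so that sufficiency could mean the reading center's judgement rather than IDx-DR's.

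**Conclusion.** The point holds for sensitivity. The stated 80% belongs to 200 eyes with both a gradable reference standard and an IDx-DR result, while the plan guarantees only 200 eyes by the reading center's count. If enrolment ends near that minimum, 80% is not assured, and from a 9% loss down to 100 analysed eyes it is not reached at any n. The likely size is a few points: 78.0% at 10% loss and 76.6% at 15%.

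This rests on three assumptions: the loss rate, which the documents do not give; enrolment ending close to 200 positives; and independent eyes, as in the plan's tables. Correlation between fellow eyes is a separate matter. Specificity would be exposed only if negatives stayed near 140, which the plan does not expect. The finding warrants a clarification of the power statement and the monitoring count, not a redesign.

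**What to change.** 1. In SAP Supplementary Tables 3 and 4 and protocol Supplementary Table 8, state that the 80% for sensitivity applies to 200 eyes with both a gradable reference standard and an IDx-DR result. Add the sensitivity power at 5%, 10% and 15% loss: 79.4%, 78.0% and 76.6%.
2. In protocol 7.4, give the masked statistician a per-eye yes/no flag for whether IDx-DR returned a result, without the positive or negative output. Strata can then be projected on analysable eyes within the planned maximum.

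The cost is a few table rows, a sentence in each document and one extra field in the monitoring data feed. The stated power becomes slightly less favourable. The flag shows no diagnosis, so masking to IDx-DR diagnoses is kept.

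Raising the minimum is not needed to resolve the point and would not be cheap. Keeping 200 analysed positives at 10% loss takes 200/0.90, or 223 eyes. At 1:4, the extra 23 positives mean about 23 × 5 = 115 more eyes, or 58 subjects, against the stated maximum of 282.
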